**9.B.13 General statistical analysis plan.** The study team has extensive experience presenting analyses from longitudinal data and includes strong biostatistical expertise (**[name] and [name]**). We are confident that we will use rigorous and up-to-date inferential methods, while retaining interpretability of the analysis and results. For each aim and hypothesis, we will pre-specify the outcome measure and time point, and the predictors of interest. Models will include the stratification variables for the randomization (consumption level and quitting history). Models will control for a standard set of potential confounders, including age, gender, race/ethnicity, peer and family influences, addiction level, and presence of anxiety disorders. Primary analyses will use logistic regression, a linear, or generalized linear model depending on whether the outcome of interest is binary, continuous or ordinal-scaled. When using data across time points, if needed, we will use a random effects model or generalized estimating equations to control for within subject correlation, in a repeated measures framework. **Power and sample size** With 450 subjects we will have 150 in each arm, Standard US pack (ST), Plain pack (PP), and Plain pack+Graphic warning (Australian Model: AM). We assume 20% dropout, occurring uniformly over the study period. For each outcome measure, the primary effects of interest are the contrasts ST-(PP and AM) and PP-AM, with the expectation that the AM effect will be larger than the PP. We conducted power analysis for the contrast with the smallest sample sizes (PP-AM), using a Fisher exact test or a 2 sample t-test for comparison of effects at the end of study; and, for comparison of in within-subject trends over time, by simulation using a generalized linear mixed effects models (GLMM). We aimed to estimate the effect size we can detect with 80% power, using a 2-sided test of hypothesis at significance level 0.025 to correct for the 2 primary contrasts of interest. For a longitudinal change measured over the three-month intervention period, results from 1000 simulations suggest power >0.85 for expected medium effect sizes in mean differences.

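### The 0.025 level in the power statement is the only correction given for the two primary contrasts; naming Holm's procedure for the final tests would recover some power at the same error rate

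*Protocol*

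**What the plan says.** Section 9.B.13 (General statistical analysis plan) states that, for every outcome measure, "the primary effects of interest are the contrasts ST-(PP and AM) and PP-AM". On size it says "With 450 subjects we will have 150 in each arm" and "We assume 20% dropout, occurring uniformly over the study period". The power analysis was done on PP-AM because that contrast has the smaller sample. Its target was the effect detectable with 80% power, and the same sentence gives the level for that calculation: "using a 2-sided test of hypothesis at significance level 0.025 to correct for the 2 primary contrasts of interest". For longitudinal change during the intervention it adds that "results from 1000 simulations suggest power >0.85 for expected medium effect sizes in mean differences".

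The part of 9.B.13 that describes the models and covariates gives no significance level and no multiple-testing procedure. Neither Bonferroni nor Holm is named anywhere in the protocol.

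**The concern.** Taken at face value, 0.025 per contrast is an equal Bonferroni split of 5%. Holm's procedure tests the smaller of the two p-values at 0.025 and, if that is significant, the other at 0.05. It holds the familywise error at 5% or less under every configuration and rejects everything the fixed split rejects.

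The advantage appears when both contrasts are truly non-zero, which is what the protocol expects: section 6 (Primary Aim 1) hypothesises the ordering AM > PP > ST, and 9.B.13 expects a larger effect for AM than for PP. If a fixed 0.025 became the final rule, a PP-AM result with a p-value between 0.025 and 0.05 would be declared non-significant even when the pooled contrast had already been established. PP-AM is the comparison closest to Primary Aim 2, which asks what the graphic warning adds to the plain pack.

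**Working it through.** **Inputs from 9.B.13.** 150 per arm; 20% dropout, so 150 × 0.8 = 120 analysed per arm at the end of study; two contrasts; two-sided 0.025; 80% power target.

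**Assumption.** The protocol speaks of medium effects without a number. The effects below, in SD units over ST, are therefore assumed and shown over a range.

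**The plan's own figures.**
- Level: 0.05 / 2 = 0.025, reproduced exactly. For two independent tests the familywise error is 1 − 0.975² = 0.0494.
- Detectable PP-AM effect at 80% power: (2.241 + 0.842) × √(2/120) = 3.083 × 0.1291 = 0.398 SD.
- If medium means 0.5 SD, a two-sample t-test at 0.025 has 94.6% power. This is consistent with the stated figure above 0.85. The protocol's simulation cannot be rerun, because its effect size, variance and correlation are not given.

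**Holm against a fixed 0.025.** With equal arms the two contrasts are orthogonal, so their powers can be multiplied. Write P1(a) for the power of ST against the mean of PP and AM (standard error √(1/120 + 1/240) = 0.1118 SD) and P2(a) for the power of PP-AM (standard error √(2/120) = 0.1291 SD), both from the noncentral t.
- Holm power for PP-AM = P2(0.025) + [P2(0.05) − P2(0.025)] × P1(0.025)
- Both significant, fixed split = P1(0.025) × P2(0.025)
- Both significant, Holm = P1(0.025) × P2(0.05) + P1(0.05) × P2(0.025) − P1(0.025) × P2(0.025)

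For PP = 0.2 and AM = 0.6, the pooled effect is (0.2 + 0.6)/2 = 0.4 and PP-AM is 0.4. Then P1 = 0.907 at 0.025 and 0.946 at 0.05; P2 = 0.800 and 0.870.
- PP-AM under Holm: 0.800 + (0.870 − 0.800) × 0.907 = 0.863
- Both, fixed split: 0.907 × 0.800 = 0.726
- Both, Holm: 0.907 × 0.870 + 0.946 × 0.800 − 0.726 = 0.820

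Power in percent, fixed 0.025 → Holm:

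| PP / AM over ST (SD) | PP-AM | Pooled contrast | Both significant |
|---|---|---|---|
| 0.2 / 0.6 | 80.0 → 86.3 | 90.7 → 93.8 | 72.6 → 82.0 |
| 0.3 / 0.6 | 52.8 → 63.4 | 96.2 → 97.1 | 50.8 → 62.4 |
| 0.2 / 0.5 | 52.8 → 61.8 | 81.0 → 84.6 | 42.8 → 55.3 |
| 0.2 / 0.7 | 94.6 → 97.0 | 96.2 → 97.9 | 91.0 → 95.1 |
| 0 / 0.4 | 80.0 → 82.2 | 32.3 → 40.9 | 25.8 → 36.7 |

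If the pooled contrast is truly null, P1(0.025) = 0.025. The PP-AM gain at 0.4 SD is then (0.870 − 0.800) × 0.025 = 0.0018, about 0.2 of a point.

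**Error rate.** In 400,000 simulated trials the familywise error was 4.9% under the global null, where Holm and the fixed split make at least one rejection in exactly the same trials. When only PP-AM was null, Holm's error was 5.0%.

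**The case against.** The strongest objection is that the protocol does not say the final tests will use a fixed 0.025. The figure stands in a sentence about the detectable effect, and a trial planning to use Holm would normally also be sized at 0.025, because that is the only level guaranteed at the first step. The testing procedure could properly be left to a statistical analysis plan that is not shown. This stands. A reader might infer that the protocol commits to testing each contrast at 0.025 come what may; the text does not support that. It remains true that this is the only correction the document states and that it sits in the section on general statistical analysis.

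Second, an equal split is a legitimate choice: it controls the error and pairs naturally with 97.5% confidence intervals. This also stands, so nothing here is a mistake.

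Third, the gain depends on assumed effects and on the pooled contrast being rejected. With PP-AM at 0.5 SD, one reading of a medium effect, power is already about 95% and Holm adds at most 2.4 points. This stands as a limit on size. The stated power above 0.85, however, refers to medium effects and does not address a smaller PP-AM difference or the chance that both contrasts succeed.

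Finally, PP-AM should not be presented as the protocol's key contrast. The protocol lists both contrasts as primary and sized PP-AM only because its sample is smaller.

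**Conclusion.** The point holds as an optional improvement. The 0.025 split is valid, and the document contains no error here. If the split is carried into the final tests, it gives up power that Holm would recover at the same 5% familywise error. That control applies within each outcome only, under either method.

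With 120 analysed per arm, the PP-AM gain is about 6 points at assumed effects of 0.2 and 0.6 SD, 9 to 11 points where PP-AM is 0.3 SD, about 2 points where it is 0.5 SD, and close to zero if the pooled contrast is null. The chance that both contrasts are significant rises by about 9 to 13 points in the first three scenarios and by about 4 points at 0.2 and 0.7 SD. One could describe the gain as worth about 20 more participants per arm, since 86% power at 0.025 for 0.4 SD needs about 140 per arm, but that equivalence belongs to the first scenario only. The direction, never a loss, does not depend on the assumed effects; the size does.

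**What to change.** Keep 0.025 in the power statement as the conservative level. Add one sentence to 9.B.13 (and to the statistical analysis plan, if there is one): the two primary contrasts of each outcome will be tested with Holm's procedure at a familywise two-sided level of 0.05, the smaller p-value at 0.025 and, if it is significant, the other at 0.05. Fix this before any unblinded analysis. If an existing analysis plan already specifies a step-down test, the sentence only brings the protocol into line with it.

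The cost is one sentence and no extra participants. The downside is that simple 97.5% intervals will not match every Holm decision: a contrast significant at the second step with a p-value between 0.025 and 0.05 will have a 97.5% interval that includes zero. The intervals can still be reported, with a note saying so.

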#### **9.B.14 Timeline**

We anticipate publishing a series of papers in the academic literature, and the project team will hold biweekly meetings (inviting wide participation) to discuss progress and seek feedback. The project PIs will prepare quarterly progress reports. Study results will be presented in national and international scientific meetings.

### **10. HUMAN SUBJECTS**

Participants enrolled in this study will be drawn from daily smokers in San Diego County. The study will randomize 450 community dwelling daily smokers, otherwise healthy, aged from 21-50 years. The study population will not include special classes of patients (e.g., fetuses, neonates, pregnant women, children,

prisoners, and institutionalized individuals). The study will have a run-in period of one month and participants will need to demonstrate that they can comply with study assessment procedures before they will be eligible to be randomized into the study groups.

**Inclusion Criteria:**

- 21-50 years of age
- A current resident of San Diego County
- Daily smokers of at least 5 cigarettes/day who are classified as in the precontemplator stage of change (i.e. do not intend to quit smoking in the next 6-months)
- Regular smokers of the five most popular US cigarette brands
- Have a cell phone with unlimited text messaging service

**Exclusion Criteria:**

- Non-Daily cigarette smokers and daily smokers of alternative brand cigarettes
- Marked organic impairment or unstable medical problems (such as a seizure disorder)
- Current pregnancy or intent to become pregnant during the next 12 weeks.

## **11. RECRUITMENT AND PROCEDURES PREPARATORY TO RESEARCH**

Study personnel will recruit 450 current smokers who use one of the five most popular brands of cigarettes as their usual brand and who live in the San Diego area. Standard media announcements for this study including print, online bulletin boards, social media, website and community outreach strategies will be used to recruit. We also have ongoing collaborations through research funded by the California Tobacco Related Disease Research Program (21XT-0076, PI: [name]) and recruitment access within UCSD Family Medicine clinics serving approximately 30,000 patients through more than 150,000 office visits. At the initial contact, assessors will describe the new study and will obtain verbal consent to enroll. Those who consent to enroll will be screened, invited to attend a baseline study visit, and directed to the web-based baseline survey after verification of electronic contact information. Participants will be given a unique ID and password to access the online survey. Informed consent to complete each survey will be imbedded into the online survey form. Written informed consent will be obtained at the initial study visit with consent procedures approved by UCSD IRB. Additional contacts (to remind participants to complete surveys) will be made via different modes including email, phone and text messaging.

## **12. INFORMED CONSENT**

Participants will provide informed consent in person. Informed consent will be obtained in writing, and the research assistant will explain the consent procedures. The informed consent document will explain in simple terms, before the participant is entered into the study, the risks and benefits to the participant. The informed consent document will contain a statement that the consent is freely given, that the participant is aware of the risks and benefits of entering the study, and that the participant is free to withdraw from the study at any time. Consent will be obtained after a thorough explanation of the study by research staff and an opportunity for the participant to ask questions about the study. The IRB-approved consent form will be signed and dated by the participant and investigator. The signed informed consent document will be retained with study records. Each participant will be given a copy of his or her signed informed consent. He/she will also be given a letter from the investigators with such information as to how to schedule appointments and how to reach the investigators.

## **13. ALTERNATIVES TO STUDY PARTICIPATION**

The alternative to study participation is to not participate.

#### **14. POTENTIAL RISKS**

The study will provide an incentive for the smoker to purchase their cigarettes from the study team rather than from a vendor in the community. This price reduction may make it less likely that the individual will quit smoking during the three months of the active intervention. Based on the experiences of the investigative team in research with smokers not intending to quit, we estimate that smokers who report that they do not intend to quit in the next 6 months have 0.03 chance of making a successful change during this time period. The price decrease is estimated to reduce this probability of 0.027 over a limited 3 month period. We expect that this will be outweighed by the effects of the change in package design for two of the study groups, as both the plain packs group and the plain packs with large warning labels groups are expected to be much more influenced to quit by the package design features of the study. We will provide ongoing monitoring of plans to quit as described below. Should a participant wish to quit smoking at any point during the study they will be provided with options of receiving print or electronic materials describing strategies to quit smoking ('Clearing the Air') and sources of smoking cessation services including no-cost services available through the California Smokers Helpline.

During the clinic visit, the participant will be observed with Kinect and Leap motion video camera sensors and recordings will be captured throughout the behavioral assessment portion of the interview. Prior to the interview, the participant will be informed that this is done to capture their interactions with the marketing materials. The text of the informed consent will include a clear explanation that any images obtained from the video will not be used outside of the study setting unless there is additional informed consent.

There is little likelihood of any physical, social or legal risk as a result of participation in this research project. There is a slight possibility that participants might be psychologically stressed from completing the web-based surveys. The consent language imbedded in the web-based survey will remind participants that they may skip over any question that they are uncomfortable answering, and that they may stop the survey at any time and/or withdraw from the study at any time without penalty.

There are potential risks to confidentiality if the security of the relational databases should be compromised. These databases will be password protected as described above and reside on an access-controlled virtual local area network kept in a secure site within the Moores UCSD Cancer Center. The potential risks to participants from this research are thought to be minimal.

#### **15. RISK MANAGEMENT PROCEDURES AND ADEQUACY OF RESOURCES**

Prior to each weekly purchase of cigarettes from the study team, we will ask the smoker's readiness to quit. Participants also will be given instructions to use text messaging tools to contact study staff at any time for information about quitting or referral to smoking cessation services. Information about cessation services is available via print material, website links, phone contact information via text message, and access to an on-call clinical psychologist on the study staff. Should a person express any desire to quit, this will be recorded as a potential endpoint (possible successful quit) and the patient will be provided with a list of a broad range of available cessation services in the San Diego community, provided with access to NCI's Clearing the Air booklet and directed to contact the no-cost California Smokers Helpline for assistance in quitting. Data containing participant identifiers (if any) will be securely stored and protected from theft and/or exposure by the use of passwords and encryption (when data are stored electronically) and locked cabinets (when the data are stored on any other transportable medium). Maximum effort will be applied to store as little sensitive information as possible on any portable hardware. All study materials will be kept in locked files in locked file rooms with exclusive access by study staff only. All results and correspondence produced from this study will only describe patient results in aggregate. Any individual patient material in a physical medium will be shredded at the end of the study. Patient level data will not be disclosed, copied, or transmitted in total or in part to anyone not connected with the approved protocol.

It is considered highly unlikely that there will be any adverse health events during this study. In the event of an error or adverse event during the study period, we will notify the Data Safety and Monitoring Committee of the Moores UCSD Cancer Center and follow their recommendations who will have the responsibility to rectify the situation or assess harm.

#### **16. PRIVACY AND CONFIDENTIALITY CONSIDERATIONS INCLUDING DATA ACCESS AND MANAGEMENT**

Data collection methods will include data obtained specifically for research purposes, including: web-based surveys and study assessment questionnaires; electronic text message questionnaires; digital images captured during video assessment interviews and saliva specimens for cotinine analysis. In addition, participants will utilize a study specific vendor website for purchasing of cigarette study product and will be prompted to purchase using text messaging on mobile phones. We will also make use of existing records and data, including: tobacco education materials and materials from publications and presentations.

Information collected from participants will be coded in a manner that precludes their identification. Data collected using survey, text message, and digital image files will be stored in locked file cabinets; with documentation containing identifying information kept separately from data that is coded by identification numbers. The roster linking participants with their identification number will be stored in a file drawer separate from the survey, text message, and image files. All data collected and entered into the computer will be identified only by a coded identification number and email accounts generated by study personnel.

Data that is collected via web and text messaging will be subject to additional security measures. Physical access to the computers will be restricted and conform to the security standards of UCSD and Moores Cancer Center. Participant data will be encrypted and will utilize a granular permissions model incorporating context-based, role-based and user-based access and authentication controls, as specified by the HIPAA Privacy and Security Rules, as well as industry-standard best practices. System Logs will track various types of system access including, but not limited to, “log in,” “communication,” “data view,” and “data modification” events. Electronic Protected Health Information (ePHI) will be isolated (e.g. 18 types of identifiers) and de-identified from coded research data such that only users with sufficient privileges (e.g. project staff in the participant contact role) will have access to confidential, personal information. All confidential, personal patient-reported information will be housed on Moores Cancer Center secured machines. All data will be backed up daily.

#### **17. POTENTIAL BENEFITS**

Participants will be contributing to scientific knowledge about the impact of cigarette packaging interventions on risk perception and associated cigarette use and quitting behaviors. This research will aid national governments, states, and communities in determining which cigarette health warning and packaging interventions are most effective in reducing tobacco use and increasing quitting behavior while also providing them with evidence-based regulatory science in support of policy decisions for tobacco control and use reduction. Study participants may benefit significantly from what we learn regarding influences on smoking behavior. In view of the substantial potential benefits and the minimal risk involved, the risk/benefit ratio is highly favorable.

#### **18. RISK/BENEFIT RATIO**

The risks to participants are judged to be acceptable relative to the anticipated benefits. By participating in this project, participants may benefit from the comprehensive behavioral assessment of their smoking patterns. If participants elect to quit smoking, withdrawal symptoms during smoking cessation may be unpleasant, but the health benefits to participants of successfully remaining abstinent are substantial. Consequently, the risk to benefit ratio in the proposed study appears to be acceptable.

## 19. EXPENSE TO PARTICIPANT

There will be no expense for participation except for providing transportation to the study site.

## 20. COMPENSATION FOR PARTICIPATION

Participants will be compensated \$20 if they successfully complete the initial baseline visit and provide a saliva sample during the run-in period. During run-in they will purchase their usual brand of cigarettes at a 10% discount from the study vendor. Following randomization, they will continue to purchase discounted cigarettes but with packaging according to study design for the intervention period; however, should they miss a scheduled purchasing point and indicate that they have purchased their usual brand elsewhere, they will be offered an additional discount to incentivize them to get back on the study protocol. After completion of the intervention period, smokers will no longer have access to discounted cigarettes from the study vendor. At 5 and 12 months, participants will receive \$40 for completion an additional web-based survey and provision of a saliva sample at each of these assessments. Finally, if they have completed all assessments in the study, they will receive an additional \$60 at the end of the study. Thus, the total incentive for all participants in the study, regardless of study arm, will be \$160.

